# Immersive virtual reality as analgesia for women during hysterosalpingography: study protocol for a randomized controlled trial

**DOI:** 10.1186/s13063-019-4023-y

**Published:** 2020-01-20

**Keywords:** Hysterosalpingography, Analgesia, Virtual reality, Pilot study

## Abstract

**Background:**

Hysterosalpingography (HSG) is an accepted radiologic diagnostic modality for initial infertility workup, and is generally considered uncomfortable and painful. However, the management of pain related to HSG remains inefficient. As an emerging nonpharmacologic and noninvasive pain control strategy, virtual reality (VR) distraction has been successfully used in areas such as burns, blunt force trauma, hospital-based needle procedures, dental/periodontal procedures, and urological endoscopy patients. This study aims to evaluate the analgesic effect of VR during HSG.

**Methods/design:**

A single-center, parallel-group, randomized controlled trial will be carried out in the Radiology Department of Yinchuan Women and Children Healthcare Hospital, Yinchuan. A total of 200 participants who are scheduled for HSG will be enrolled in this study. The participants will be randomized (1:1) into two groups: a VR group and a blank control group. The VR group will receive routine care plus immersive VR intervention and the blank control group will receive routine care. Outcomes will be monitored at baseline, immediately after HSG and 15 min after HSG for each group. The primary outcome is the worst pain score during HSG by a visual analog scale (VAS). The secondary outcomes include: affective pain, cognitive pain, and anxiety during the HSG procedure; worst pain within 15 min after HSG; patient satisfaction and acceptance with pain management; physiological parameters; adverse effects; HSG results; and immersion perception score of the VR system (for the VR condition only).

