### Sample size determination

The worst pain severity as the primary end-point measure is employed to estimate sample size in the current research according to previous studies on physical therapy for pediatric burn injury pain and dentalgia pain [19, 24]. According to our previous study on breakthrough pain [26], we used a pilot trial to determine the sample size. Fourteen subjects recruited in May 2019 were invited to the pilot trial. Seven of them were included in the VR intervention group during HSG, and worst pain scores of two parallel groups were recorded at T1. The sample size calculation formula is based on a two-group, parallel controlled design:
$$ \mathrm{n}=\frac{\left({{\mathrm{q}}_1}^{-1}+{q_2}^{-1}\right){\left({t}_{\alpha /2}+{t}_{\beta}\right)}^2{\sigma_c}^2}{\delta^2} $$where *n* represents the total sample size of the whole study, *σ*_c_ represents the standard deviation, *δ* represents the between-group difference with clinical significance, and q1 and q2 are the sample size ratio of the two groups (q1 = q2 = 0.5). According to the preliminary test, the worst pain score experienced during HSG reported by all blank control group participants (*n* = 7) revealed a mean (standard deviation (SD)) of 6.50 (2.26) out of 10. Participants (*n* = 7) in VR group reported a mean (SD) of 5.61 (0.93). The standard deviation of the whole sample (*n* = 14) was 1.72. At an *α* value of 0.05, a power of 90% (β = 0.10), and given a two-tailed test, we obtained *σ*_c_ = 1.72, *δ* =  ∣ *μ*_1_ − *μ*_2_∣ = 0.89. These data were used to calculate the value of the overall parameter to enter into the formula, and an *n* value of 157.02 was obtained. Thus, the rounded total sample size of the two groups was 158 (79 participants in each group). Allowing for a 20% dropout rate and withdrawals before study completion, we decided to enroll a total of 190 participants (95 participants in each group).

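### The abstract enrols 200 and the sample-size section 190, with nothing to reconcile them; 190, the only derived total, falls short of the protocol's own 158 evaluable at 20% loss

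*Protocol article*

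**What the plan says.** In the abstract (Methods/design) the article states: "A total of 200 participants who are scheduled for HSG will be enrolled in this study". Allocation is 1:1. The abstract gives no number per group and no basis for the total.

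The section Sample size determination gives a full chain. A pilot of 14 women supplies the standard deviation ("The standard deviation of the whole sample (*n* = 14) was 1.72") and a between-group difference of 0.89. With two-sided alpha 0.05 and 90% power, a "value of 157.02 was obtained", and "the rounded total sample size of the two groups was 158 (79 participants in each group". A 20% allowance for dropout and withdrawal is then applied, after which "we decided to enroll a total of 190 participants (95 participants in each group".

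No other section settles the total. Study setting mentions the target sample size without a number. Randomization, allocation concealment and blinding says that the sequences are generated in advance but not how long they are.

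**The concern.** Both statements describe enrolment, so this is not an enrolled figure set beside an evaluable one; the evaluable figure is a third number, 158. The planned total fixes the length of the allocation list, the point at which recruitment ends, and the power claim, so it should have one value.

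The natural repair would be to treat 190 as correct and 200 as a slip in the abstract. That repair is not clean, because 190 does not deliver what the sample-size section says it delivers. Someone has to decide which total applies and show how it was reached.

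**Working it through.** **Inputs, all from Sample size determination unless noted:** SD 1.72; difference 6.50 - 5.61 = 0.89; two-sided alpha 0.05; power 90%; q1 = q2 = 0.5; evaluable total 158; loss 20%; enrolment 190. Enrolment 200 is from the abstract.

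**1. Reproduce the evaluable number.** With q1 = q2 = 0.5 the factor (1/q1 + 1/q2) is 4, so

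n = 4 x (1.96 + 1.282)² x 1.72² / 0.89² = 4 x 10.5106 x 2.9584 / 0.7921 = 157.02.

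This matches the stated value. Rounding up to an even total gives 158, or 79 per group, also as stated.

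**2. Find where 190 comes from.**

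- Multiplying: 158 x 1.20 = 189.6, rounded up to 190. This is the protocol's figure.
- Dividing: 158 / (1 - 0.20) = 197.5, rounded up to 198 (99 per group). This is the number that leaves 158 after 20% are lost.

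**3. Try to find where 200 comes from.** Neither route gives 200. Adding the 14 pilot women to 190 gives 204, so that does not explain it either.

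**4. Apply the stated 20% loss to each total.** Under the normal approximation, power = Φ(0.89 x √(N/4) / 1.72 - 1.96), where N is the evaluable total.

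| Enrolled | Evaluable at 20% loss | Power at 20% loss | Power with no loss | Loss tolerated before falling below 158 |
|---|---|---|---|---|
| 190 | 190 x 0.8 = 152 | Φ(1.230) = 89.1% | 94.6% | 1 - 158/190 = 16.8% |
| 200 | 200 x 0.8 = 160 | Φ(1.313) = 90.5% | 95.5% | 1 - 158/200 = 21.0% |

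The noncentral t distribution gives 88.7% and 90.2% at 20% loss, so the picture is the same.

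**5. Size of a misuse that two totals might invite.** Suppose the data were tested at 190 and, if not significant, again at 200, each time at |Z| > 1.96. The two statistics have correlation √(190/200) = 0.975. By simulation the overall two-sided type I error is then about 6.0% instead of 5.0%. This is an illustration only.

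**The case against.** The best defence is that only 190 is derived, with formula, inputs and a split per group, whereas 200 appears once in an abstract with no support. A reader would normally take the derived Methods figure as operative. The power gap is little more than one percentage point at 20% loss. The primary outcome is collected immediately after a procedure of about 20 minutes, so a full 20% loss is pessimistic. The analysis also includes all randomised participants with multiple imputation. All of this stands and limits the weight of the point. It does not remove the conflict, because the derived figure misses its own requirement under the loss that the protocol itself assumes.

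A reader might infer three stronger things, and the article supports none of them:

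- **That the trial has two legitimate stopping points and an inflated type I error.** The 6.0% requires an unplanned second test. Data monitoring says that no interim analyses are planned, Statistical analysis assigns the work to a blinded statistician outside the trial, and the sequences are generated in advance. Participants and staff are unblinded, but that does not imply a comparative look at the data.
- **That 200 is the intended, correctly inflated number.** Correct inflation gives 198. That 200 exceeds 198 does not show that it was derived this way, and nothing in the article links 200 to the dropout step.
- **That the registry entry disagrees.** The registry record is not available here, so nothing can be said about it.

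**Conclusion.** The point holds as an unreconciled inconsistency in a core design figure: 200 in the abstract and 190 in the sample-size section, a difference of 10 women. It is compounded by the fact that 190 leaves 152 evaluable at the stated 20% loss, 6 short of the protocol's own 158 and at about 89% instead of 90% power. The total of 200 would meet the requirement (160 evaluable, about 90%) but has no stated derivation.

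The practical effect on power is small, and neither total threatens the primary analysis. These figures take the protocol's SD of 1.72 and difference of 0.89 as given and count lost women as contributing nothing. Any type I error consequence is hypothetical.

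**What to change.** State one enrolment target, with its derivation, in both the abstract and Sample size determination. Use that number as the length of the randomisation list, and say that recruitment stops there.

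- **If 190 is kept:** correct the abstract to 190 (95 per group), and in the sample-size section restate either the loss tolerated (about 16.8% for 158 evaluable) or the power at 20% loss (about 89%).
- **If 200 is kept:** correct the sample-size section to 100 per group, and show that it covers 158 / 0.8 = 197.5, rounded up to 198.

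The cost is a wording correction and, if 200 is chosen, the 10 extra women that the abstract already announces. Study setting reports about 1000 procedures a year. Trial status gives 22 recruited at submission, so neither total had been approached at that time.

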**Discussion:**

This study will focus on exploring a simply operated, noninvasive and low-cost analgesia during the HSG procedure. The results of this trial will provide data on the feasibility and safety of VR distraction therapy during HSG.

**Trial registration:**

Chinese Clinical Trial Register, ChiCTR1900021342. Registered on 16 February 2019.

## Background

Infertility is clinically defined as 1 year of attempted conception that has not resulted in pregnancy; it is one of the most prevalent chronic health defects impacting young couples [1]. Approximately 6.6–26.4% [2] of couples of reproductive age are confronted with infertility in the industrialized nations. The primary physiological factors leading to female infertility are fallopian tube abnormalities, accounting for about 30–40% [3]. Hysterosalpingography (HSG) is an accepted radiologic diagnostic modality for initial infertility workup which can assess the patency of the fallopian tube and the womb cavity situation [4].

HSG is a minimally invasive gynecological procedure performed in the outpatient department which is generally considered to be uncomfortable and painful. It has been reported that 85% of women suffer operation pain, with half complaining of moderate to severe pain [5, 6]. Currently, it is generally believed that the pain related to HSG is mainly caused by cervical instrumentation, uterine instillation of contrast material, peritoneal irritation secondary to contrast material spill, or delayed postoperative pain due to prostaglandin release [7]. The uncomfortable and painful experience of the operation can lead to a high degree of stress, poor compliance with HSG procedures, and an unwillingness to undertake other similar diagnostic investigations [8]. It is very important to find an ideal analgesic method that can provide adequate pain control in the absence of significant adverse reactions.

Various interventions have been assessed to decrease pain and increase patient compliance during HSG, including paracetamol [9], nonsteroidal anti-inflammatory drugs such as fenoprofen and naproxen, opioid analgesics such as tramadol [10], intracervical and intrauterine topical anesthetic [5, 6, 11, 12], and a paracervical block utilizing lignocaine. Although studies have shown that these analgesics have certain effects on HSG pain relief, Ahmad et al. [7] conducted a systematic review and meta-analysis of related randomized controlled trials and reported that there is no consensus concerning the optimal analgesic or timing of its administration. Furthermore, in our institution, no analgesic guideline exists to direct the gynecologists to prescribe analgesics and no effort has been made to enhance gynecologist use of analgesia. As a result, patients receive no analgesics during HSG as routine care in our institution.

Nonpharmaceutical therapy, including music therapy, hypnosis, massage and distraction, can significantly improve the patient experience while undergoing painful medical procedures [13, 14]. Researchers have recently proposed that immersive virtual reality (VR) can be applied as an unusually powerful psychological therapy for acute pain relief [15]. The essence of immersive VR is the user’s illusion of going inside the three-dimensional computer-generated world through a head-mounted device, as if the virtual world is a place the user is visiting [16]. Hoffman et al. proved that VR can relieve pain caused by blunt instrument injury [17] and wound debridement as well as dressing burn injuries [15]. Furman et al. [18] conducted clinical trials on dental surgery patients, showing that VR effectively alleviates pain and fear of dental surgery.

To date, and to the best of our knowledge, no study has examined the effect of VR intervention on women undergoing HSG. This clinical randomized controlled trial aims to evaluate whether VR intervention, when compared with a blank control group, could decrease pain and to evaluate the effects of pain relief on the ease of performing HSG for infertility diagnosis.

## Methods/design

### Study design

The primary objective of this single-center, parallel-group, randomized controlled trial is to find out the clinical analgesic effect of VR intervention in patients during HSG compared with a blank control group. The secondary objectives of this trial include comparing the anxiety level during HSG between the two groups, evaluating the safety of clinical use of VR by recording adverse effects and physiological indexes, assessing patient acceptance for the nonpharmaceutical analgesia therapy and investigating the satisfaction of patients with VR.

The trial has been approved by the Institutional Ethics Committee of Ningxia Medical University (reference no. 2018–233). This randomized controlled trial has been registered in the Chinese Clinical Trial Registry (ChiCTR1900021342). The whole study design is illustrated in Fig. 1. Additionally, a Standard Protocol Items: Recommendations for Interventional Trials (SPIRIT) figure for the schedule of enrolment, interventions, and assessments is presented in Fig. 2. We will conduct the protocol of this trial according to the SPIRIT guidelines (see Additional file 1).

**Fig. 1 Fig1:**
[figure not shown]
Study design framework. BC blank control, BP blood pressure, GRS graphic rating scale, HSG hysterosalpingography, P pulse, SpO_2_ oxygen saturation, VAS visual analog scale, VR virtual reality

**Fig. 2 Fig2:**
[figure not shown]
SPIRIT schedule of enrolment, interventions, and assessments. BP blood pressure, GRS graphic rating scale, HSG hysterosalpingography, P pulse, SpO_2_ oxygen saturation, T0 baseline, T1 immediately after HSG, T2 15 min after HSG, VAS visual analog scale

### Study setting

This study will be conducted in the HSG room of the Radiology Department of Yinchuan Women and Children Healthcare Hospital in Ningxia province. This institution is an urban, public, tertiary-care teaching hospital, specializing in maternal care and childcare in Ningxia Hui Autonomous Region located in Northwest China. Annually 50,000 patients undergo treatment at the fertility clinic and approximately 1000 HSG are performed every year in this institution. It is therefore feasible to reach the target sample size in this selected clinical setting. We expect to complete recruitment within 10 months.

### Study participants

Women will be recruited into the study according to the following inclusion criteria: 1) indications for HSG including infertility, recurrent miscarriage, and other miscellaneous reasons [5]; 2) aged 20–45 years; 3) willing to participate in the study and sign informed consent; and 4) no signs of pain before HSG.

The exclusion criteria are: 1) use of antidepressants or sedatives; 2) presence of psychiatric disorders; 3) recent receipt of analgesics within 6 h; 4) allergy to contrast medium or iodine; 5) a recent history of acute pelvic inflammatory disease; 6) visual acuity <1.0 or hearing abnormity; 7) susceptible to motion sickness; 8) operator difficulty due to cervical adhesion or congenital variation, or completing the examination after multiple operations.

In the Radiology Department, the HSG procedure will be carried out on each weekday by two gynecology assistants (both female who have worked in the HSG room for >10 years). The results of the HSG will be analyzed by a Chief Radiologist (who has worked in the HSG room for >10 years). These two gynecology assistants will receive training from the protocol conceiver.

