### Recruitment

Recruitment will take place in the Radiology Department of Yinchuan Women and Children Healthcare Hospital. Participants for the study will be recruited through WeChat advertising and posters in the infertility clinic. After patients arrive at the Radiology Department they will be screened with a free preliminary physical examination and a check against the inclusion/exclusion criteria. The potential participants will receive information about the aims, benefits, and latent risks of the study from the protocol designer. If the patients wish to participate, they will be asked to sign an informed consent form that they agree to participate in the study and are willing to let the protocol designer publicize the research results, including pictures. Participants are entitled to withdraw from the study at any time and this will not prejudice their subsequent treatment. The whole process of recruitment follows the principle of respect for autonomy.

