### Randomization, allocation concealment and blinding

A simple random sampling method will be used in our study. Patients who are scheduled for HSG and meet the eligibility criteria will be randomly allocated into either the blank control group or the VR group at a 1:1 ratio. The randomization sequences will be generated in advance with a computerized random number generator (random.org). This is performed by a statistical expert who is not involved in this trial. A sealed opaque envelope will be used to store the randomization sequences of all allocations. The random number table will be kept confidential by the full-time secretary of this project. Baseline data will be recorded as close to immediately before the HSG procedure as possible. After baseline data collection, the allocation will be revealed. Blinding is not feasible.

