### Interventions

In the blank control arm, gynecology assistants will perform the whole procedure as they usually would. In the VR group, the immersive VR system will be provided (Fig. 4). After placing the patient in the lithotomy position, the trained investigator will help the patient wear the specific helmet and teach them how to interact with the virtual world through gaze-based tracking and the wireless controllers. The gynecology assistant will carry out the relevant operation 2 min later. VR distraction will be applied during the whole procedure. Patients in the VR group will be asked how many virtual scenes they ‘enter’ to monitor adherence to intervention protocols.

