### Statistical analysis

In this study, all data will be collected by a specialized researcher. A blinded statistician who is not involved in this trial will perform statistical analysis using SPSS version 22.0 (Chicago, IL, USA). A complete statistical analysis plan will be generated in advance by the trial statistician. All randomized participants should be included in the analysis, and missing data will be handled using multiple imputation. Data will be analyzed initially on an intention-to-treat basis. For comparing the primary outcome between the two parallel groups, additional per-protocol analysis will be performed, and reasons for any protocol violations will be reported. We will consider all *P* values <0.05 to be statistically significant.

Descriptive statistics will be used to describe the demographic features by means (SD), medians (interquartile ranges; minimum to maximum), and proportions (exact binomial 95% confidence intervals). A *t* test will be applied to determine the differences between the primary outcome. Secondary outcomes such as the amount of time spent thinking about pain, pain unpleasantness, worst pain within 15 min after HSG, anxiety, satisfaction, and acceptance with pain management will use *t* tests or Mann–Whitney tests. Chi-squared tests or Fisher’s exact test will be used for HSG results and adverse reactions. When comparing the physiological parameters, the repeated measures analysis of variance will be used. Pearson correlation analysis will be used to analyze the relationship between immersion perception score of the VR system and the three pain dimensions.

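### Exclusion criterion 8 includes events known only during or after the HSG, so it permits unblinded exclusion after randomisation and conflicts with the rule that all randomised women are analysed

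*Protocol article*

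**What the plan says.** All references are to the Protocol article.

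- **Study participants**, exclusion criterion 8: "operator difficulty due to cervical adhesion or congenital variation, or completing the examination after multiple operations".
- **Recruitment**: on arrival at the Radiology Department, "they will be screened with a free preliminary physical examination and a check against the inclusion/exclusion criteria".
- **Randomization, allocation concealment and blinding**: scheduled patients who "meet the eligibility criteria will be randomly allocated into either the blank control group or the VR group at a 1:1 ratio". Baseline data are taken just before the HSG. Then: "After baseline data collection, the allocation will be revealed". On masking: "Blinding is not feasible".
- **Interventions**: in the VR arm the helmet is fitted and its use taught first. "The gynecology assistant will carry out the relevant operation 2 min later".
- **Hysterosalpingography procedures**: a tenaculum is used only where the catheter proves hard to insert, so difficulty is met at insertion.
- **Statistical analysis**: "All randomized participants should be included in the analysis", with multiple imputation for missing data, intention to treat first, and an additional per-protocol analysis of the primary outcome.

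**The concern.** An exclusion criterion should be decidable before randomisation. Parts of criterion 8 are not. If a woman meets it once her HSG is under way, the eligibility section says she should not be in the trial and the analysis section says she should be analysed. Both rules cannot hold for her.

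The primary outcome is worst pain during the HSG, and the Background lists cervical instrumentation among the main causes of HSG pain. It is a reasonable inference, though the article does not say so, that difficult insertions score higher. Excluding them would condition the primary comparison on an event that follows allocation, judged when the arm is known. If removal differed between arms, the randomised comparison would be distorted. If such a woman's score were discarded and treated as missing, imputation would draw on the easier procedures and would not undo the selection.

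**Working it through.** **Order of events, from the sections listed above**

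1. Arrival, preliminary examination and check of the criteria.
2. Randomisation of women who meet the criteria.
3. Baseline data, then allocation revealed, with no blinding.
4. In the VR arm, helmet fitted; the operator starts 2 minutes later.
5. Catheter insertion, where difficulty is met.
6. End of the HSG, when it is known whether multiple operations were needed.
7. Worst pain recorded immediately after the procedure.

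Criterion 8 is meant for step 1. Adhesion or a congenital variation may be known then. Difficulty met by the operator belongs to step 5, and completion after multiple operations, read plainly, to step 6. The criterion therefore cannot be fully applied at the only point where the article says the criteria are checked.

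**The plan's own figure** (Sample size determination). With equal groups, SD 1.72, difference 0.89, two-sided 5% and 90% power:

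n = 4 × (1.96 + 1.282)² × 1.72² / 0.89² = 4 × 10.5106 × 2.9584 / 0.7921 = 157.02

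This reproduces the stated value and gives 158 (79 per arm). The 0.89 serves below as the yardstick.

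**Illustration of bias.** The article gives no rate of difficult procedures, no pain increment and no removal rates, so all three are assumed. Suppose no true effect, the same share p of difficult procedures in both arms, and scores D points higher in those procedures. If an arm removes a fraction f of them, the mean of those retained is raised above the easy-procedure mean by

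m(f) = D × p × (1 − f) / (1 − p × f)

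The spurious VR benefit is m(f control) − m(f VR). Example with p = 10%, D = 2, half removed in control and all in VR: 2 × 0.10 × 0.5 / 0.95 − 0 = 0.105, or 12% of 0.89.

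| p | D | removed 25% control, 75% VR | removed 50% control, 100% VR | removed 0% control, 100% VR |
|---|---|---|---|---|
| 5% | 1 | 0.025 | 0.026 | 0.05 |
| 5% | 3 | 0.075 | 0.077 | 0.15 |
| 10% | 2 | 0.100 | 0.105 | 0.20 |
| 15% | 1 | 0.075 | 0.081 | 0.15 |
| 15% | 3 | 0.224 | 0.243 | 0.45 |

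The range is 0.025 to 0.45 points, or 0.025/0.89 = 3% to 0.45/0.89 = 51% of the planned difference. Swapping the arms reverses the sign. Equal removal gives zero in this model, though it narrows the population.

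**Illustration of power.** Enrolling 95 per arm with 20% dropout leaves 76, with power 89.1% for 0.89 and SD 1.72. If exclusions came on top of that dropout, a further 5%, 10%, 15% or 20% would give 87.5%, 85.7%, 83.7% or 81.4%. If they fell within the 20% allowance, there would be no further loss.

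**The case against.** The strongest reply is that the article already contains the safeguard. Criteria are checked on arrival, only eligible women are randomised, and all randomised women are analysed by intention to treat first. Nothing in the article provides for withdrawing a woman under criterion 8 after randomisation, and nobody is named as applying it. A reader might infer that operators who know the arm will remove the most painful procedures and so bias the main result. The article does not support that: if the analysis rule governs, the main analysis drops nobody. What stands is that the two printed rules conflict, that the article does not say which prevails, and that the per-protocol analysis remains exposed.

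Three further objections have force.

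- Adhesion or a congenital variation may be known from history or the preliminary examination, and the phrase about multiple operations is awkward and might refer to earlier attempts. The first is right, and those conditions can stay in the criterion. The second is possible, but the wording does not say it and would need correcting in any case.
- The size rests wholly on assumed inputs, and the largest values need complete removal in one arm and none in the other. This is correct, so the figures only illustrate.
- The Background also aims to "evaluate the effects of pain relief on the ease of performing HSG for infertility diagnosis", and one might argue that criterion 8 removes the women who bear most on that aim. Ease of the procedure is not among the stated objectives or outcomes, so the point should not rest on it.

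**Conclusion.** The point holds as an inconsistency that permits unblinded exclusion after randomisation. It does not show that such exclusion will occur or that the primary result will be biased. The conflict rests on the order of events in the article and needs no outside figure. That difficult procedures are more painful is an inference from the Background and the procedure description.

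The size and direction of any bias are unknown. Under the assumptions shown it runs from about 0.03 to 0.45 points on the 0 to 10 scale; with 10% difficult procedures scoring 2 points higher, it is 0.10 to 0.20. It is nil in this model if removal is equal in both arms, but nothing in the article ensures equality when the arm is known. The correction should be made because it is nearly free and because outcome scores that are never collected cannot be recovered later.

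**What to change.** - Limit criterion 8 to conditions documented before randomisation, from history or the preliminary examination.
- Delete difficulty met during the procedure, and completion after multiple operations, as grounds for exclusion.
- State that women found difficult during HSG stay in the intention-to-treat analysis with their observed scores, and are not dropped from the per-protocol set for difficulty alone.
- Report difficult procedures descriptively by arm, for example number of insertion attempts and tenaculum use. Do not adjust for these or restrict on them: they arise after randomisation, and doing so would repeat the problem.
- The Trial status section reports 22 women recruited at submission. Identify any already excluded under criterion 8 after randomisation and report them by arm.

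The cost is a change of wording and two fields on the case form. The small downside is slightly more variable pain scores, because difficult procedures stay in.
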